### Data handling

The investigators and co-investigators will make every reasonable effort to protect the confidentiality of the patients participating in the trial. Patients will not be identified by name, social security number, address, telephone number, or any other direct personal identifier. A unique identification code will be assigned to each patient participating in this trial. Information about the code will be kept in a secure location. Data storage will reside at the coordinating site, MMC, in locked offices. Sites will retain collected data for a minimum of 15 years. All electronic data will be password-protected on computers stored in locked offices. Access to patient information will be limited to trial personnel only.

### Sample size

Sample size estimation is based on a “responder” analysis, as recommended by the Initiative on Methods, Measurement and Pain Assessment in Clinical Trials (IMMPACT) Group recommendations [21]. Effect sizes were estimated on the basis of published academic literature. Neurectomy is considered successful in 70% [13, 22–25]. Regarding the potential efficacy of PRF treatment, a mean effect size was estimated at 30%. There is no available academic literature apart from two case reports on the use of PRF in ACNES patients. The targeted effect size is a difference in proportion responding to treatment (neurectomy versus PRF) of 40%; i.e., 70% responding in neurectomy the group versus 30% in the PRF group. Using G*Power 3.1.7 software, 80% power and a two-tailed alpha of 5%, 58 participants are needed to demonstrate a potential effect of either type of treatment on pain relief. With an allowance for attrition of 10% in both arms at 6-month follow-up, we will aim to recruit a total of 66 patients.

### Randomization

After enrollment and completing the baseline questionnaires, patients are randomly assigned (1:1 – PRF:neurectomy) to one of two treatment groups following a computer-generated list of random numbers by blocks of 8. Randomization is stratified by treatment site location (Boxmeer or Veldhoven). The allocation sequence is concealed from the enrolling researcher and assessing participants in sequentially numbered, opaque and sealed envelopes, prepared by a secretary with no involvement in the trial. One central coordinating investigator (RM) is responsible for enrolling patients and is the only investigator allowed to inform the independent secretary of newly enrolled patients.

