### Blinding

Blinding of patients, surgeons and pain specialists is not possible due to the characteristics of both treatments (minimally invasive treatment without general anesthesia versus invasive treatment with the use of general anesthesia).

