### Recruitment

Potential patients are identified by physicians who are working in abdominal pain clinics at the SolviMáx or the Maasziekenhuis Pantein and are screened for eligibility. Patients are then informed on the purpose, nature and duration of the trial. Following consultation, potential participants are allowed 14 days for consideration. If a patient subsequently consents, they are then randomized by the principal investigator. Patients are allowed to withdraw their consent at any given time during the study period.

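### A single fixed block size of 8 within each site, in an unblinded trial with one enroller, makes part of the allocation sequence predictable, and the text leaves open who opens the envelope

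*Protocol article*

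**What the plan says.** All places are in the Methods of the Protocol article.

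- **Ratio and blocks (Randomization):** "patients are randomly assigned (1:1 – PRF:neurectomy) to one of two treatment groups", "following a computer-generated list of random numbers by blocks of 8". Only one block size is given.
- **Strata (Randomization):** "Randomization is stratified by treatment site location (Boxmeer or Veldhoven").
- **Concealment (Randomization):** the sequence is kept from the enrolling researcher in "sequentially numbered, opaque and sealed envelopes, prepared by a secretary with no involvement in the trial". Assignment follows enrolment and the baseline questionnaires.
- **Enroller (Randomization):** one central coordinating investigator "is responsible for enrolling patients and is the only investigator allowed to inform the independent secretary of newly enrolled patients".
- **Who randomises (Recruitment):** "If a patient subsequently consents, they are then randomized by the principal investigator".
- **Blinding:** "Blinding of patients, surgeons and pain specialists is not possible due to the characteristics of both treatments".

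The Trial status section shows that recruitment was still open when the article appeared in August 2017.

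**The concern.** Sealed envelopes hide the next card. They do not hide what can be deduced by counting. With a 1:1 ratio, each block of 8 holds four assignments to pulsed radiofrequency (PRF) and four to neurectomy. Treatment is open, so earlier assignments can be known. All enrolment passes through one investigator, who is therefore placed to follow the sequence at both sites. Once four patients in a block have received one arm, the rest of that block is fixed.

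An enroller who can foresee the arm may, even without intending it, influence who is enrolled next or when. The design leaves some room for this. Some exclusion criteria involve judgement (impaired communication, other chronic pain syndromes), and candidates have up to 14 days to decide. The arms differ greatly in burden (a needle procedure under local anaesthesia against surgery under general anaesthesia), and the primary outcome is self-rated pain. Selection on unrecorded prognosis would bias the comparison, and adjusting for recorded baseline variables would remove only part of that bias.

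Separately, the text does not settle who carries out the randomisation step. Randomization has the enroller notify an independent secretary, whereas Recruitment says that the principal investigator randomises. Neither section says who opens the envelope.

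**Working it through.** The article gives no figure for predictability, so there is none to reproduce.

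**Inputs from the document:** block size 8, ratio 1:1, two site strata, and a recruitment target of 66 (Sample size).
**Assumptions:** the guesser knows the block size and all earlier assignments at that site. The split of the 66 patients between sites is not given, so a range is shown.

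**Step 1: allocations that are certain in a complete block.** There are C(8,4) = 70 equally likely orderings. An allocation is certain when one arm has already been used four times in the block. Counting over the 70 orderings:

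| Position in block | Orderings in which it is certain | Probability |
|---|---|---|
| 1 to 4 | 0 | 0% |
| 5 | 2 | 2.9% |
| 6 | 10 | 14.3% |
| 7 | 30 | 42.9% |
| 8 | 70 | 100% |

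Expected number per block = (2 + 10 + 30 + 70)/70 = 112/70 = 1.6, and 1.6/8 = 20%.

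**Step 2: best guess.** The guesser always names the arm with more places left and tosses a coin when they are equal. Enumeration of the 70 orderings gives 373/70 = 5.33 correct out of 8, or 66.6%, against 4 of 8 (50%) by chance.

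**Step 3: applied to 66 patients.** Because 66 is not a multiple of 8, some blocks stay incomplete. Two splits mark the ends of the range:

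- 33 and 33: each site has four complete blocks plus one patient, so 2 × 4 × 1.6 = 12.8 certain.
- 13 and 53: one and six complete blocks, each followed by five patients, so 7 × 1.6 + 2 × 0.029 = 11.3 certain.

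Over all splits from 6/60 to 60/6, between 11.3 and 12.8 allocations are certain, and 43 to 44 are guessed correctly (33 by chance).

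**Step 4: effect of varying the block size.** This is a simulation with 33 patients per site (assumed). The guesser makes optimal use of the history and knows the set of possible sizes, but not the size of the current block.

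| Block sizes | Certain | Best guess correct |
|---|---|---|
| 8, fixed | 19% | 66% |
| 2, 4, 6 | 4% | 69.5% |
| 4, 8 | 7% | 67% |
| 4, 6, 8 | 2.4% | 67% |
| 6, 8, 10 | 1.7% | 65.6% |

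The fixed-8 row is 6.4/33 = 19.4%, slightly below 20%, because the last block at each site is incomplete. Varying the size removes most of the certainty at block ends but hardly changes the average advantage from guessing. Sizes that are all below 8 make that advantage larger.

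**Step 5: who randomises.** Set side by side, the two sections can be read together if the principal investigator only starts the step by notifying the secretary. They conflict if the principal investigator is also the enroller and opens the envelope, because the sequence is meant to be concealed from the enrolling researcher. The text does not say which applies. This bears on concealment and does not change the figures in Steps 1 to 4.

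**The case against.** The case for the plan is substantial. The list is computer-generated, and the envelopes are "sequentially numbered, opaque and sealed envelopes, prepared by a secretary with no involvement in the trial". Assignment comes after enrolment and baseline questionnaires. A fixed block of 8 is already less predictable than a fixed block of 6 (25% certain, 68.3% guessed) or of 4 (33% certain, 70.8% guessed). Clinic physicians, not only the enroller, identify and screen candidates, which narrows the route to steering. The article condenses a fuller protocol in which envelope handling may be described. All of this stands, and it limits the size of the point. It does not remove it, because none of these safeguards stops a count of the assignments already made.

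A reader might infer more than the document supports:

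- **That upcoming allocations are predictable in general.** About 80% are not certain beforehand, and the first four in a block never are.
- **That the enroller does keep a tally, or that bias has occurred.** The document says neither. The figures are what such a tally would yield.
- **That publishing the block size during recruitment created the problem.** It adds little, since the trial team would already know its own block size.
- **That Randomization and Recruitment contradict each other.** This is an ambiguity. Whether the coordinating and principal investigators are the same person is not stated, nor is who opens the envelope.

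**Conclusion.** The point holds in a limited form. A single block size of 8 within site, open treatment and one enroller together make the sequence partly predictable: 20% of allocations are certain in a complete block, which is about 11 to 13 of 66 patients, and the best guess is right about 67% of the time. These figures assume knowledge of the block size and of all earlier assignments at the site. The document places the enroller where that knowledge could be gathered, but does not show that it was. The statements on who randomises are unclear and should be reconciled. The sample size is not affected. The change is worth making because it is cheap, and because the outcome is self-rated and unblinded.

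**What to change.** 1. For patients not yet allocated at each site, have the independent secretary generate a new list with randomly varying block sizes that are not disclosed to investigators and not all smaller than 8, for example 6, 8 and 10. With 33 patients per site assumed, certain allocations fall to about 2%. The general guessing advantage stays at about 65-66%, so this is a reduction and not a cure.
2. Reconcile the Randomization and Recruitment sections. State that the independent secretary, not an investigator, opens the next envelope, and only after enrolment and the baseline questionnaires are complete.

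**Cost:** a regenerated list and a short amendment. The largest possible end-of-trial imbalance between arms rises slightly. It is half the largest block per site, so over two sites 2 × 4 = 8 with blocks of 8 and 2 × 5 = 10 when the largest block is 10, plus at most whatever an old block left unfinished at the switch adds. The new list protects only the patients still to be allocated. Enrolment began in October 2015 and the trial was expected to end in December 2017, so that may be few. The clarification of who opens the envelope is worth making in any case.

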### Blinding

Blinding of patients, surgeons and pain specialists is not possible due to the characteristics of both treatments (minimally invasive treatment without general anesthesia versus invasive treatment with the use of general anesthesia).

### Statistical methods

All analyses are performed using the Statistical Package for the Social Sciences (SPSS) version 21 for Windows. Categorical variables are described as frequencies. Continuous data are tested for normality and are presented as means with standard deviation (±SD) or median values (range) as appropriate. The primary outcome measure is pain relief using the NPRS as compared to the preintervention pain levels (t_0_). Data of the PRF and neurectomy groups will be compared using the Student’s *t* test or the Wilcoxon signed-rank test, as appropriate. Secondary outcomes will be compared between groups at various time points (baseline, 8-week follow-up and 6-month follow-up). They will be compared to preintervention values using Student’s *t* test or the Wilcoxon signed-rank test as appropriate. A *p* value < 0.05 is considered significant. Analysis of data will be done as randomized (the intention-to-treat analysis) and secondary “as-treated.”

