### Outcomes

The primary objective is to compare the effect of PRF with a neurectomy in terms of pain relief at the 8-week follow-up. The outcome is measured using the Numeric Pain Rating Scale (NPRS, 0 = no pain and 10 = excruciating). Pain is measured at t_0,_ before intervention and 8 weeks after allowing the determination of short-term efficacy (t_1_) as shown in the schedule of enrollment, interventions and assessments, according to the SPIRIT Statement (Fig. 3). Long-term efficacy is measured at 6-month follow-up (t_2_). Success is defined as more than 50% NPRS pain reduction following intervention.

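### The sample size is built on responder proportions, but the named primary test compares NPRS values, so the stated 80% power does not describe that test

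*Protocol article*

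**What the plan says.** Three sections of the protocol article bear on the primary comparison.

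- **Sample size.** "Sample size estimation is based on a “responder” analysis". "The targeted effect size is a difference in proportion responding to treatment (neurectomy versus PRF) of 40" percent, that is, "70% responding in neurectomy the group versus 30% in the PRF group". The result is stated as "80% power and a two-tailed alpha of 5%, 58 participants are needed", raised to 66 for attrition.
- **Outcomes.** Pain is scored on the 0 to 10 NPRS before treatment (t0) and at 8 weeks, which is the time point of the primary objective. The section adds: "Success is defined as more than 50% NPRS pain reduction following intervention". It does not say whether success or the score itself is the primary variable.
- **Statistical methods.** "The primary outcome measure is pain relief using the NPRS as compared to the preintervention pain levels" (t0). The two arms are then compared by Student's t test or the Wilcoxon signed-rank test. On categorical data the section says only: "Categorical variables are described as frequencies".

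No chi-square, Fisher or other test of proportions is named anywhere in the article, and no mean NPRS difference or SD is given.

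**The concern.** A power statement belongs to one endpoint, one effect and one test. Here the effect is a difference between two proportions, while the test named for the primary outcome works on NPRS values. The endpoint that justifies the sample size has no named test, and the endpoint that has a named test has no stated effect, spread or power.

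What is at stake is the reading of the result. A responder comparison and a comparison of NPRS change can differ in significance in a trial of this size. The trial is unblinded and the outcome is reported by the patient. The article also says that the result may bring PRF into the treatment algorithm. The primary variable and its test therefore need to be beyond dispute before the data are analysed.

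**Working it through.** **Inputs.** From Sample size: response rates 0.70 and 0.30, two-sided alpha 0.05, power 0.80, 58 patients before attrition, 10% attrition, 66 to recruit. From Randomization: 1:1 allocation, hence 29 per arm. The t-test effect sizes below are assumptions, because the article gives none.

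**1. Reproducing 58 as a two-proportion calculation.** With mean rate 0.5 and difference 0.4:

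n = [1.960 × √(2 × 0.5 × 0.5) + 0.842 × √(0.7 × 0.3 + 0.3 × 0.7)]² / 0.4² = (1.386 + 0.545)² / 0.16 = 23.3, so 24 per arm (48 in total) without continuity correction.

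With continuity correction: n′ = (23.3 / 4) × [1 + √(1 + 4 / (23.3 × 0.4))]² = 28.1, so **29 per arm, 58 in total**.

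Exact power of the two-sided Fisher test at 0.70 against 0.30, by enumeration of all outcomes:

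| Per arm | Fisher power |
|---|---|
| 28 | 79.0% |
| 29 | 81.4% |
| 30 | 83.8% |
| 33 | 89.5% |

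Both routes fit 58. For attrition, 29 / 0.9 = 32.2, so 33 per arm and 66 in total. The plan's arithmetic reproduces, and it is that of a test of proportions.

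**2. Power of the t test that is named.** With 29 per arm there are 56 degrees of freedom and the critical value is about 2.00. The noncentrality is d × √(29 / 2) = 3.81 × d, where d is the between-arm difference in NPRS change divided by its SD.

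| Assumed d | Noncentrality | Power at 29 per arm |
|---|---|---|
| 0.5 | 1.90 | 46.5% |
| 0.6 | 2.28 | 61.2% |
| 0.75 | 2.86 | 80.1% |
| 0.8 | 3.05 | 84.9% |
| 1.0 | 3.81 | 96.3% |
| 1.05 | 3.99 | 97.5% |

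The last row is the case in which 70% and 30% arise from two normal distributions of equal variance cut at the same threshold: d = z(0.70) − z(0.30) = 0.524 + 0.524 = 1.05. The article does not say that this model holds, and it gives nothing from which another d could be derived.

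**The case against.** **The article is a condensed text, and the full protocol or analysis plan may name a test of proportions.** That could explain why none appears here. It does not remove the mismatch: the Statistical methods section does not defer the matter but names the primary measure and its tests, and these do not fit the Sample size section.

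**Pain relief may be meant as responder status.** Then the t test and the rank test are not the natural tests for a yes/no outcome, and the section would still need correcting.

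**A reader might infer that the responder endpoint will never be tested.** The text does not go that far. The sentence on frequencies stands beside the rule for means and medians and concerns how data are presented. What can be said is that no test of proportions is named.

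**A reader might infer that the trial is underpowered.** This is not shown. Under the normal-shift assumption the named t test would have 97.5% power, more than Fisher's test. Its power is unstated, which is different from too low.

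**A reader might infer that the plan leaves the primary outcome open, with a material gain in false positives from choosing between two results.** Read literally, the Statistical methods section does fix NPRS pain relief as primary; the trouble is that the sample size was not built for it. How often the two analyses would disagree, and how far choosing between them would raise the type I error, depends on an NPRS distribution that the article does not give, so no figure is offered here.

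**Conclusion.** The point holds as a contradiction between two stated rules. The 80% power and the 58 patients belong to a comparison of responder proportions; the primary test named in Statistical methods is a different test on a different scale, and its power is not defined by anything in the article. On assumed standardized differences from 0.5 to 1.05, that power spans 46.5% to 97.5%, with 80% reached at about 0.75.

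The Fisher figure of 81.4% rests only on the plan's own rates and on 29 evaluable patients per arm. The t-test range rests on assumed effects and a normal outcome. The number of patients is not in question. Because the primary test itself is affected, the two sections should be reconciled before analysis.

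The rank test named is one for paired data, which is a separate fault in the same sentence; this point does not depend on it.

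**What to change.** Align Statistical methods with Sample size. State as the primary endpoint the proportion of patients with more than 50% NPRS reduction from t0 at 8 weeks, analysed by intention to treat. Compare the arms by a two-sided Fisher exact test at 5%, and report the risk difference with its 95% confidence interval. Keep the between-arm comparison of continuous NPRS as a named supportive analysis.

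The alternative is equally valid in form: keep NPRS pain relief as primary, and restate the power for that test with the mean difference and SD it assumes. The responder comparison then becomes the named supportive analysis.

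The first option changes wording only. The sample size stays at 58 evaluable and 66 recruited. The second needs a justified difference and SD, and whether 58 is then enough depends on them. As the article describes the trial as still recruiting, either change should be made as a dated amendment before the outcome data are analysed.

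### The NPRS comparison between arms is planned without baseline NPRS as a covariate and without the site stratum, which gives up precision of uncertain size but causes no bias

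*Protocol article*

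**What the plan says.** Under Statistical methods, the article defines the outcome and names the test. The outcome is given as "The primary outcome measure is pain relief using the NPRS as compared to the preintervention pain levels". On the comparison it states: "Data of the PRF and neurectomy groups will be compared using the Student’s" t test, with the Wilcoxon signed-rank test as the alternative. Neither test takes a covariate or a stratum, and the section mentions no adjusted model.

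Both adjusting variables will be on file. Under Outcomes, NPRS is recorded "before intervention and 8 weeks after allowing the determination of short-term efficacy". Under Randomization, "patients are randomly assigned (1:1 – PRF:neurectomy) to one of two treatment groups following a computer-generated list of random numbers by blocks of 8", and "Randomization is stratified by treatment site location (Boxmeer or Veldhoven").

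The sample size has a different basis: "Sample size estimation is based on a “responder” analysis", with "70% responding in neurectomy the group versus 30% in the PRF group".

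**The concern.** A change score uses the baseline by subtraction, which fixes its coefficient at 1 whatever the data show. Unless the regression slope of 8-week NPRS on baseline NPRS happens to be 1, this leaves in the estimate noise that a fitted coefficient would remove. It also lets part of any chance difference in baseline pain pass into the estimated treatment effect. With about 29 evaluable patients per arm, chance differences of a quarter of an SD are ordinary.

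Stratifying by site balances the arms within each hospital. An analysis that ignores site leaves any difference between hospitals in the residual variance, so the standard error is too large if the hospitals differ.

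At stake is the width of the confidence interval for the mean NPRS difference, and for the secondary scales measured at baseline.

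**Working it through.** **1. The plan's own figure.** Inputs from Sample size: 70% versus 30%, 80% power, two-sided alpha of 5%.

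- Uncorrected pooled formula: n = [1.96·√(2·0.5·0.5) + 0.8416·√(0.21 + 0.21)]² / 0.40² = 23.3, so 24 per arm (48 in total).
- With continuity correction: (23.3/4)·[1 + √(1 + 4/(23.3·0.40))]² = 28.1, so 29 per arm, or 58. Fisher exact power by enumeration at 29 per arm is 81.4%.
- Attrition: 29/0.90 = 32.2, so 33 per arm, or 66.

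The 58 and 66 reproduce. They rest on responder proportions, so nothing below changes them.

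**2. Variance of the two estimators.** Assume that relief means absolute change. Let r be the correlation between baseline and 8-week NPRS, and k the 8-week SD divided by the baseline SD. The article gives neither, so both are assumptions. With the baseline SD set to 1:

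- change score: 1 + k² − 2rk
- ANCOVA: k²(1 − r²)
- ratio, ANCOVA to change score: k²(1 − r²) / (1 + k² − 2rk)

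At k = 1 the ratio reduces to (1 + r)/2. It equals 1, meaning no gain, when rk = 1, because the ANCOVA slope is then exactly 1.

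| r | k = 1 | k = 1.5 | k = 2 |
|---|---|---|---|
| 0.2 | 0.600 | 0.815 | 0.914 |
| 0.3 | 0.650 | 0.871 | 0.958 |
| 0.5 | 0.750 | 0.964 | 1.000 |
| 0.6 | 0.800 | 0.993 | 0.985 |

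Example at k = 1.5, r = 0.3: 2.25·0.91 / (3.25 − 0.90) = 2.0475/2.35 = 0.871.

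The variance saving over r = 0.2 to 0.6 is therefore 20–40% at k = 1, about 1–18% at k = 1.5 and about 0–9% at k = 2.

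**3. The same in power.** Take an effect that the change-score test detects with 80% power at 29 per arm. ANCOVA power is Φ(2.80/√ratio − 1.96). At r = 0.3 this gives 93.5% (k = 1), 85.1% (k = 1.5) and 81.7% (k = 2). At r = 0.5 it gives 89.9%, 81.4% and 80.0%. A simulation at 58 patients with k = 1 and no site effect, comparing the change-score t test with ANCOVA on baseline and site, gave 78% against 92% at r = 0.3 and 79% against 87% at r = 0.5. This agrees with the formula once small-sample degrees of freedom are counted.

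**4. Chance baseline imbalance.** The standard error of the difference in baseline means is SD·√(2/29) = 0.26 SD. Given an observed imbalance d, the change-score estimate moves by (1 − rk)·d. At r = 0.5 that is half of d when k = 1, a quarter when k = 1.5 and nothing when k = 2.

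**5. Site.** The article gives no site effect. Purely as an illustration, if site explained 10% of outcome variance, the true two-sided alpha of the unadjusted test would be about 2·[1 − Φ(1.96/√0.90)] = 0.039, below the nominal 0.05. If site explained nothing, alpha would stay at 0.05. The direction is conservative, and the size cannot be computed from the document.

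**The case against.** The strongest reply is that an unadjusted comparison in a randomised trial is a valid choice. That stands. A reader might infer from the point about imbalance that the planned t test is biased, but the document does not support this: averaged over randomisations the estimate is unbiased, and its standard error already covers chance imbalance.

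A second reply concerns size. A reader might quote the 20–40% saving, equivalent to 1/0.80 − 1 = 25% up to 1/0.60 − 1 = 67% more patients, as the general result. Those figures hold only for equal SDs at baseline and 8 weeks, which the article does not report. Its planning assumption makes each arm a mixture of responders and non-responders, and such a mixture may well spread the follow-up scores. At k = 1.5 or 2 most of the saving disappears. This reply also stands. In addition, the article does not say that relief means absolute change; if it means percentage relief or response, the ratio does not apply.

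A third reply is that covariates are left to an analysis plan. This carries less weight, because the article does name the primary test, so the unadjusted comparison is a stated choice. The alternative it names is also unsuited to the task: a signed-rank test compares paired values, not two independent arms.

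Finally, ANCOVA models means, whereas the plan provides for non-normal data. That is a fair reason to keep a non-parametric alternative, but it must be one for independent groups.

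**Conclusion.** The point holds in a limited form. The stated NPRS comparison uses neither baseline NPRS as a covariate nor the site stratum, and its non-parametric option is a paired test. The cost is lost precision and avoidable sensitivity to chance baseline differences. Over assumed r of 0.2 to 0.6 and k of 1 to 2, the variance saving available runs from 40% down to nothing, so no single figure should be quoted. The direction is secure: apart from a few degrees of freedom, ANCOVA is not less precise than the change score. The gain from site is unknown and may be near zero.

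Two further inferences should be resisted. Leaving site out does not inflate the type I error; at worst it makes the test conservative. Nor is the sample size wrong: 58 and 66 reproduce, and the gain concerns only the mean-NPRS comparison. This is a worthwhile improvement to a valid analysis.

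**What to change.** Reword Statistical methods as follows.

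- Analyse 8-week NPRS by ANCOVA with arm, baseline NPRS and site, and report the adjusted difference with its 95% CI.
- Use the same model for secondary scales analysed as continuous scores: SF-12, PDI, BPI, and DN4 only if it is analysed as a score and not as a classification.
- For the outcome of more than 50% reduction, report a site-stratified (Mantel-Haenszel) risk difference with its 95% CI.
- If a non-parametric alternative is kept for the comparison of arms, name one for independent groups, such as the Wilcoxon rank-sum test.

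No new data, visits or patients are needed, since baseline NPRS and site are already recorded. The cost is wording and a few degrees of freedom. The article reports recruitment as ongoing, so the model can still be fixed before the data are analysed. In an unblinded trial this also avoids choosing covariates after the results are seen.

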## Methods

### Trial design

This prospective, multicentre, non-blinded, proof-of-concept, randomized controlled trial (with a one-way optional crossover at 8 weeks) is performed in the SolviMáx Center of Expertise for ACNES and Center of Excellence for Abdominal Wall and Groin Pain and Maasziekenhuis Pantein, Boxmeer, The Netherlands. SolviMáx is a subdivision of the Surgical Department of Máxima Medical Center (MMC), a teaching hospital situated in the southern part of The Netherlands. The Dutch Ministry of Health, Welfare and Sport has certified SolviMáx as a Center of Expertise for ACNES treatment. The trial will be based on a clinical proof-of-concept design in order to investigate a potential difference in pain relief following either PRF treatment or an anterior neurectomy in ACNES. Furthermore, it is designed to attain more knowledge on the use of PRF on peripheral nerves and to detect possible side effects.

The present trial follows the guidelines of the Declaration of Helsinki (version 19 October, 2013). The protocol (protocol number NL53171.015.15) is approved by the Medical Ethics Committee of MMC. The study protocol (version 1) is registered at www.trialregister.nl (NTR registration number: 5131, date of registration 15 April 2015). The present paper is written according to the Standard Protocol Items: Recommendations for Interventional Trials (SPIRIT) 2013 Statement for reporting a clinical trial protocol [12]. The SPIRIT Checklist is provided as Additional file 1.

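### The non-parametric test named for comparing the two randomised arms on the primary outcome is a paired test, and the arms contain no pairs

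*Protocol article*

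**What the plan says.** All references are to the protocol article.

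- **Outcomes:** "The primary objective is to compare the effect of PRF with a neurectomy in terms of pain relief at the 8-week follow-up".
- **Statistical methods, primary outcome:** "The primary outcome measure is pain relief using the NPRS as compared to the preintervention pain levels". The next sentence gives the test: "Data of the PRF and neurectomy groups will be compared using the Student’s *t* test or the Wilcoxon signed-rank test, as appropriate". Continuous data are first tested for normality, and *as appropriate* is the only rule for choosing between the two tests.
- **Statistical methods, secondary outcomes:** these are to be compared between groups at several time points, with no test named in that sentence. Then, against baseline: "They will be compared to preintervention values using Student’s *t* test or the Wilcoxon signed-rank test as appropriate".
- **Randomization:** "patients are randomly assigned (1:1 – PRF:neurectomy) to one of two treatment groups", in blocks of 8, stratified by site.
- **Trial design:** a parallel trial "with a one-way optional crossover at 8 weeks", open only to PRF patients in whom treatment was unsuccessful.

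Neither a rank-sum nor a Mann-Whitney test is named anywhere in the article.

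**The concern.** The signed-rank test ranks differences within pairs: the same patient twice, or two matched patients. PRF and neurectomy patients are different people, and no matching is described. The crossover supplies no pairs either, because it is offered only at 8 weeks, when the primary comparison is made, and only in one direction.

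The same pair of tests is named for change from preintervention values, where the data are truly paired and the signed-rank test is suitable. The text does not separate the two uses.

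At stake is the primary p-value whenever normality is rejected. An analyst who follows the sentence literally has no defined input for the test. One who silently substitutes another test departs from the published plan in an unblinded trial. This is not detail left to a fuller document: the article names a specific test, and that test does not fit the design.

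**Working it through.** **1. The plan's own figure.** Sample size states: "Using G*Power 3.1.7 software, 80% power and a two-tailed alpha of 5%, 58 participants are needed", for 70% against 30% responders, plus 10% attrition to reach 66.
- Two independent proportions, mean 0.5, difference 0.4: n = (1.960·√(2·0.5·0.5) + 0.842·√(0.7·0.3 + 0.3·0.7))² / 0.4² = 23.3 per arm, so 24 (48 in total). This does not match.
- With continuity correction: n′ = (23.3/4)·(1 + √(1 + 4/(23.3·0.4)))² = 28.1, so 29 per arm (58 in total). This matches.
- Fisher's exact test agrees: power is 79.0% at 28 per arm and 81.4% at 29.
- Attrition: 29/0.9 = 32.2, so 33 per arm, 66 in total.

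The sample size therefore rests on two independent proportions. It treats the arms as independent and does not depend on the signed-rank test.

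**2. Can the arms be assumed equal in size?** No.
- 66 = 8·8 + 2, so with blocks of 8 in two sites at least one block stays incomplete.
- Suppose 33 per arm, each patient lost independently with probability 10%. The article gives this figure for 6 months; applying it at 8 weeks is an assumption. The chance of equal numbers remaining is Σₖ [C(33,k)·0.9ᵏ·0.1³³⁻ᵏ]² = 0.17. With 5% loss it is 0.23.

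Unequal arms are thus the usual case. Pairing across them means discarding patients, against the intention-to-treat commitment in Statistical methods.

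**3. If the arms are equal, what does arbitrary pairing do?** The article gives no SD for NPRS relief, so this is illustrative: relief normal with SD 2.5, rounded to integers, mean 3 in one arm and 3 + d in the other, 29 per arm, 4000 trials per row, patients paired in list order.

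| True difference d | Signed-rank rejects | Rank-sum rejects | Tests disagree at 0.05 |
|---|---|---|---|
| 0 | 4.0% | 4.4% | 2.6% |
| 1.5 | 58.2% | 59.0% | 8.9% |
| 2 | 81.2% | 81.9% | 5.8% |

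Other assumed shapes at 30%/70% responders gave type I error up to 5.0% and disagreement of about 6–8%.

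Re-ordering one arm of a single simulated dataset (d = 1.5, 2000 re-orderings) moved the signed-rank p from 0.00003 to 0.011, while the rank-sum p stayed at 0.0012. In another dataset, simulated under a different assumed shape, p ran from 0.03 to 0.30 (rank-sum 0.07), which crosses 0.05. These are single examples that show the mechanism; they do not show how often a verdict changes.

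**4. How often is the branch reached?** Assumed: 29 per arm, integer baseline NPRS about 7 (SD 1.5, range 4–10), 30%/70% responders. A Shapiro test rejected normality in at least one arm in:
- about 32% of trials with unimodal change, SD 2.5;
- about 39% with two normal clusters of follow-up scores;
- about 81–82% with relief spread uniformly over 50–100% in responders and 0–50% in non-responders.

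**The case against.** The strongest reply is that this is a slip of the pen for rank-sum, which any competent analyst would correct. That is quite likely. It explains the sentence but does not repair it, and nothing else in the article does.

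Four stronger readings are tempting, and the objection is right to resist them:

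- *The primary p-value as a whole is uncomputable or arbitrary.* This is true of one branch only. The same sentence offers Student's t test, which can be run for independent samples.
- *The non-parametric branch is the likely one, because the NPRS is a bounded integer score.* The article gives no NPRS mean, SD or shape, and the 30–80% range above moves with the assumption made.
- *The error inflates false positives.* It does not: under random pairing the type I error stayed at about 4–5%, and in the simulation tabulated above the loss of power was under one percentage point.
- *A within-arm test is meant to replace the randomised comparison.* The wording does not support this. Both Outcomes and Statistical methods speak of comparing PRF with neurectomy.

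What survives is narrower: the named test has no valid pairs and no unique result for this comparison.

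**Conclusion.** The point holds, limited to the non-parametric branch of the comparison between arms. There the article fixes a paired test for independent, unmatched groups. With unequal arms it cannot be run on all patients. With equal arms its p-value is a product of patient order, differing in significance from the rank-sum result in roughly 6–9% of simulated trials with a true difference. That size rests on assumed NPRS distributions and 29 per arm. The fault is a result that cannot be reproduced, not a biased one.

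The t-test branch, the sample size of 58 and 66, and the use of the signed-rank test for change from t0 all stand. Because the sentence governs the primary comparison, it should be corrected before the data are analysed.

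**What to change.** In Statistical methods:

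- In the sentence comparing the PRF and neurectomy groups, replace the Wilcoxon signed-rank test with the Wilcoxon rank-sum (Mann-Whitney U) test, and specify the independent-samples t test.
- Name the same two tests for the secondary comparisons between groups, where no test is now given.
- Keep the signed-rank or paired t test only for within-patient change from t0.

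A Hodges-Lehmann difference with 95% CI beside the rank-sum test is an optional addition and is not needed to cure the error. The cost is a short wording change: no new data and no change in sample size.
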